#### B. Safety Assessment

- 1. Adverse Events (Table 9)
- 2. Analysis (Table 10 and 11)

A.7.2. If not already addressed above, describe the plans for aggregate review of unanticipated problems (including but not limited to adverse events) across all sites, in order to monitor subject safety.

At enrollment, we will inform child care centers and their participating providers to contact the project manager if they feel an injury or illness may have occurred to them or a child in their care as a result of their participation in this study. If such an event occurs, the project manager will collect a detailed description of the event, the adverse outcome, severity of the adverse event, and whether or not participants viewed it as related to the study. This report will then be reviewed by the DSM officer, who will categorize it as: definitely unrelated, or unlikely, possibly, probably, or definitely related to study participation. Although injuries could occur as a result of an intervention that promotes regular physical activity, in our previous center-based work, no injuries related to participation were reported. We therefore anticipate that injury risk is present, but

minimal.

Adverse event reports will be submitted to the IRB after completion by the DSM officer. The PI will submit a summary of these reports to the NIDDK project officer on an annual basis. As a minimal risk study that complies with all guidelines for data and participant safety, study suspension is not anticipated. However, if such an event were to occur, the Principal Investigator would contact NIDDK immediately to report the suspension, give reasons for the suspension, and describe the plan to meet the requirements for lifting the suspension

A.7.3. What are the criteria that will be used to withdraw an INDIVIDUAL SUBJECT from this study or halt the research intervention (e.g., abnormal lab tests, allergic reactions, failure or inability to comply with study procedures, etc.)?

There are no instances where we would withdraw an individual subject from the study or halt the research intervention.

A.7.4. Are there criteria that will be used to stop the ENTIRE STUDY prematurely (e.g., safety, efficacy, unexpected adverse events, inability to recruit sufficient number of subjects, etc.)?

Yes

Please explain

Given the minimal risk associated with this intervention study, it is highly unlikely that an accumulation of excess adverse events would prompt stopping of the trial. However, as outlined elsewhere, we will monitor adverse event rates in all participants, and the DSO, together with the study investigators, will alert the IRB and the sponsor if a larger than reasonably expected injury rate should occur in the treatment group. Other issues relating to stopping rules for this trial include:

New Information

It is exceedingly unlikely that any new information comes available during this trial that would necessitate stopping the trial.

Limits of Assumptions

Difficulty in recruiting or retaining adequate numbers of participants could potentially require stopping the study. While protocols make every effort to avoid such issues, stopping rules have been created in case such an issue arises. Those rules are as follows:

failure to recruit adequate numbers of participants (red zone classification), or  
failure to retain adequate numbers of participants (red zone classification)

Suboptimal recruitment is classified as falling into one of three zones – yellow, amber, and red. Red zone classification is the most severe of these categories and is defined as less than 25% of the benchmark at the 25% time point or the 50% time point, or less than 50% of the benchmark at the 75% time point.

It is possible that excessive study dropouts and/or missing data will limit the value of data analysis of measurements. In the grant proposal, we allowed for a 20% attrition in the recruited child care centers and children. Pre-post-test differences will be evaluated in order to examine the effects on the study power and to detect differences in the primary outcome. Results will be summarized and communicated to the PI, Co-Investigators, DSO, and NIDDK.

A.7.5. Will this study involve a data and safety monitoring board or committee?

No

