## Outcome Measures and Program Evaluation

Data Collection. Outcome measures will be collected on participating child care centers, providers, and children at three time points (0, 6, and 12 months). Although the Go NAPSACC program will be implemented center-wide (available to all children and child care providers in each center), measurements will only be collected on children and child care providers formally enrolled in the study. These measures will be collected in large part during a two-day on-site visit to the child care center and supplemented with self-administered surveys. This on-site visit will be conducted by data collectors who have undergone extensive training and certification on all measurement procedures and are blinded to study-arm assignment. Identical data collection protocols will be used at each timepoint.

In addition, interviews will be conducted by phone in a 20% random sample of child care directors and providers from the Go NAPSACC+ arm at 12 months to gather information that might be useful in improving the intervention, and/or implementing the intervention in the child care setting. Topics will include preference for intervention format, length, barriers to intervention components, suggestions to improve the intervention, overall satisfaction, including the diet and PA recommendations, online trainings, and Health Educator.

A.4.3. If subjects are assigned or randomized to study "arms" or groups, describe how they are assigned.

- Describe the methods of computing the randomization schedule (if any) and maintaining blinding (if any).
- Who will perform these computations?
- How will you verify each subject's eligibility prior to randomization?

Centers will serve as the unit of randomization. Following baseline testing of each cohort, the study statistician ([name]) will randomize centers to either standard Go NAPSACC or Go NAPSACC Enhanced. Randomization tables will be created by [name] using a permuted block approach, with block sizes of 2-4 to ensure equal distribution between arms throughout the randomization period. [name] will deliver intervention assignments directly to the study coordinator, who will inform participating centers and the Health Educator delivering the intervention. Investigators (except the study statistician) and data collectors will be kept blinded.

A.4.4. Describe any follow up procedures.

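### Adverse events are captured only through unsolicited reports of suspected study-related harm, so the rates that A.7.4 relies on cannot be estimated reliably

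*Protocol*

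**What the plan says.** **How events enter the record (A.7.2).** At enrollment, centers and participating providers receive this instruction: "contact the project manager if they feel an injury or illness may have occurred to them or a child in their care as a result", where taking part in the study is the cause meant. For each report the project manager records a description, outcome and severity, and "whether or not participants viewed it as related to the study". The safety officer then classes the event as "definitely unrelated, or unlikely, possibly, probably, or definitely related to study participation".

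**What the figures are used for (A.7.4).** The plan states that "as outlined elsewhere, we will monitor adverse event rates in all participants". The safety officer and investigators will alert the IRB and the sponsor "if a larger than reasonably expected injury rate should occur in the treatment group". No expected rate or limit is given. The only reference point, in A.7.2, is that "in our previous center-based work, no injuries related to participation were reported". The safety report outline in A.7.1 and A.7.2 lists one adverse event table and two analysis tables, without saying whether they are split by arm.

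**Existing contact with participants.** Outcome data come from a two-day visit at 0, 6 and 12 months, "supplemented with self-administered surveys" (Outcome Measures and Program Evaluation). Under B.4.1, the full incentive for a time point depends on returning the surveys.

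**The concern.** A rate needs a numerator collected in a known way from a known denominator. Here the denominator is known but the numerator is filtered twice. The participant must suspect the study as the cause, and must then make contact without being asked. The fraction of injuries that passes both filters is not known and is not estimated anywhere in the plan.

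Two uses of the count suffer:

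- **The A.7.4 alert.** It sets the treatment-group rate against what would reasonably be expected. A low count could mean few injuries or few reports.
- **Any comparison of arms in the safety report.** The fraction reported may not be the same in both arms, so an apparent difference could be one of reporting, and a real one could be masked.

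Enhanced providers are asked to increase their activity, and A.6.10 names soreness and injury as possible consequences. The question is therefore not an idle one, although the expected harm is mild.

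**Working it through.** **1. The passages side by side.** A.7.2 gives one route: a participant who suspects the study makes contact. A.7.4 relies on rates in all participants and says that this monitoring is outlined elsewhere. The rest of the protocol text shown describes no collection of injuries that would give a rate. A.7.1 covers accrual, withdrawals and the outline of the safety report.

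**2. Is reporting liable to differ by arm?**

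- After randomization the centers are told their assignment (A.4.2, Randomization).
- Enhanced providers receive weekly reminders and tailored feedback for six months, and a Health Educator sees their data (A.4.2, Go NAPSACC Enhanced).
- Standard-arm providers have no direct contact with the research team outside data collection (A.4.2, Standard Go NAPSACC).
- Against this, the enrollment instruction precedes randomization and is the same in both arms, and directors in both arms have monthly check-ins for six months.

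Different reporting is therefore plausible but not established.

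**3. Size.** The protocol gives no adverse event rate, reporting fraction or alert limit, so there is no stated figure to reproduce. From the protocol: 168 teachers randomized 1:1 by center, so 168 / 2 = 84 per arm. The true risks and reporting fractions below are assumptions.

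Expected reports = 84 × true risk × fraction reported.

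*Treatment group alone, which is what A.7.4 concerns:*

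| True risk | Fraction reported | Injuries | Expected reports |
|---|---|---|---|
| 10% | 50% | 8.4 | 4.2 |
| 20% | 50% | 16.8 | 8.4 |
| 20% | 25% | 16.8 | 4.2 |
| 20% | 10% | 16.8 | 1.7 |

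The first and third rows give the same 4.2 reports although the true risk differs twofold. In the last row the chance of no report at all is (1 − 0.20 × 0.10)^84 = 0.98^84 = 18%, treating teachers as independent.

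*Between arms, which bears on the safety report and not on the A.7.4 alert.* Apparent ratio = true ratio × (Enhanced fraction reported / standard fraction reported).

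| True ratio | Standard reporting | Enhanced reporting | Apparent ratio |
|---|---|---|---|
| 1 | 20% | 50% | 1 × 0.50 / 0.20 = 2.5 |
| 1 | 25% | 50% | 1 × 0.50 / 0.25 = 2.0 |
| 2 | 50% | 25% | 2 × 0.25 / 0.50 = 1.0 |
| 2 | 25% | 50% | 2 × 0.50 / 0.25 = 4.0 |

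At a 10% risk in both arms, the first row means 84 × 0.10 × 0.50 = 4.2 reports against 84 × 0.10 × 0.20 = 1.7.

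**4. What solicited collection would buy.** Take a true rise from 10% to 20%, 84 teachers per arm, a two-sided 5% test of two proportions, and clustering ignored. Power is 44% if all injuries are captured, 23% if half are, 13% if a quarter are and 8% if a tenth are. Asking everyone does not make this a well-powered safety comparison. It removes the filter by attribution and makes the rate interpretable.

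**The case against.** The case on the other side is substantial, and several parts of it stand.

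- **Suspicion is not proof of relation.** Participants need only feel that the study may be the cause, and the officer can class a report as definitely unrelated. A reader might infer that only events accepted as study-related are counted. The text does not support that: suspicion gates the report, and the later classification does not remove it.
- **The alert is not a comparison of arms.** A.7.4 sets the treatment group against expectation. Under-reporting in the standard arm does not enter that trigger, so the between-arm figures do not test it. A reader might infer that the alert cannot work at all. That is too strong, because a cluster of volunteered injuries could still prompt it.
- **Different reporting by arm is an inference.** The common instruction and the directors' check-ins in both arms count against it, and the weekly messages are not said to ask about harm. The documents support a liability to differ, and no more.
- **Other documents may fill the gap.** The safety officers' checklist, the grant application and the teacher surveys are attachments that are not shown. The point is therefore limited to the protocol text at hand.
- **Asking about everything would create problems.** A.6.2 says that specific health conditions will not be asked about. A question on all illness would also send ordinary childhood illness among 672 children through the chain from project manager to safety officer to IRB.
- **Spontaneous reporting is proportionate for minimal risk.** This limits the weight of the point. It does not reconcile a commitment to rates with a method that cannot supply them.

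**Conclusion.** The point holds in limited form. In the protocol text shown, A.7.2 collects unsolicited reports of suspected study-related harm, while A.7.4 relies on adverse event rates in all participants and on a treatment-group injury rate. The reports are an unknown fraction of events, so those rates cannot be estimated reliably, and a by-arm comparison in the safety report is liable to reporting differences. The documents do not show that the alert is useless or that reporting will in fact differ.

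The size is unknown. Every risk and reporting fraction used above is an assumption, and only the 84 teachers per arm comes from the protocol. The primary and secondary outcomes are unaffected. Given the minimal risk described, this is a modest improvement in safety data and worth making because it costs little.

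**What to change.** Reconcile A.7.2 and A.7.4 as follows.

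1. Check whether the attached teacher surveys already contain an injury question. If not, add one identical item to the 6- and 12-month teacher surveys in both arms, asking about injuries since the last survey whether or not they are thought to be related to the study.
2. Limit the item to injuries. This avoids conflict with A.6.2 and keeps routine childhood illness out of the review chain. State whose injuries it covers, and have A.7.4 claim rates only for those participants and for injuries.
3. Use these answers for the injury rates sent to the safety officer. Keep spontaneous reports, shown separately, for prompt detection between surveys.
4. Replace the reference in A.7.4 to monitoring outlined elsewhere with a pointer to this collection. Whether and how to quantify the expected rate is for the sponsor and the safety officer to settle; no value is proposed here.

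The cost is one item at two existing time points, with no extra visits or staff. The downsides are more minor events for the safety officer to classify, reliance on six-month recall, and a first solicited answer that arrives only when each center's active phase ends. The last is the reason to keep spontaneous reporting alongside.

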#### A.4.2. Describe the study design. List and describe study procedures, including a sequential description of what subjects will be asked to do, when relevant.

The proposed study will use a cluster randomized control trial to evaluate if improving child care providers' health behaviors elicit meaningful change in dietary and PA behaviors in 2-5-year-old preschool children in their care and the child care environment. To evaluate the impact, measurements will be collected at three-time points baseline, post-intervention (6 months), and maintenance (12 months post, no contact). Measures will be collected using a combination of self-report surveys, direct observation/measurement, and interviews by trained project staff. Additionally, The Go NAPSACC Enhanced arm will include a child care provider-level weight management intervention that encourages a reduced energy diet (stop light diet [SLD]), increased PA, and regular weight monitoring. We will use commercially available applications for self-monitoring PA (Fitbit Inspire 3) and weight (Aria wireless scales).

**Randomization.** Centers will serve as the unit of randomization. Following baseline testing of each center, the study statistician ([name]) will randomize centers to either standard Go NAPSACC or Go NAPSACC Enhanced. Randomization tables will be created by [name] using a permuted block approach, with block sizes of 2-4 to ensure equal distribution between arms throughout the randomization period. [name] will deliver intervention assignments directly to the study coordinator, who will inform participating centers and the Health Educator delivering the intervention. Investigators (except the study statistician) and data collectors will be kept blinded.

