**A.8.3. Provide a compelling justification for the proposed sample size in terms of the likelihood of achieving each aim.**

Power analysis. This trial is powered to detect between group difference (Standard Go NAPSACC vs. Go NAPSACC Enhanced) of 5 units in HEI score and 1 minute per hour in non-sedentary PA. The sample size and power calculations for the proposed cluster RCT design depends on the following parameters: the number of child care centers, the number of students per school (~8; ~4 children x 2 classrooms), effect size (d), provider-level and center-level intra-class correlations (ICCs; ?), and the proportion of explained variance in school means by center-level covariates (R^2). We anticipate that on average about 8 children and 2 providers will participate at each child care center, and conservatively calculated sample size estimating 0% of variance can be accounted for by covariates. The ICCs observed in our previous work assessing preschool children's dietary intake and PA (R01 HL120969) were 0.04 and 0.07 for HEI score and 0.07 and 0.10 for non-sedentary PA at the provider- and center-levels, respectively. Based on previous studies at child care, the standard deviation of change in HEI score is estimated at 11 units and non-sedentary PA is estimated at 3 minutes per hour. Furthermore, we calculated power for each of the two primary comparisons using a type I error rate of 2.5%, thus keeping overall Type I error rate at 0.05. Sample size was initially calculated using assumptions associated with non-sedentary PA knowing that the higher ICC would require a larger sample size. This sample size was then used to conduct a power analysis for HEI score.

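### The section on early stopping permits an undefined look at primary-outcome differences, reported to investigators who are meant to stay blinded

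*Protocol*

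**What the plan says.** Section A.7.4 answers yes to the question "Are there criteria that will be used to stop the ENTIRE STUDY prematurely". Under the sub-heading on limits of assumptions it lists two stopping rules, a recruitment red zone and a retention red zone. It then notes that dropout and missing data could limit the analysis, and recalls the 20% attrition allowance for centers and children. Two sentences follow: "Pre-post-test differences will be evaluated in order to examine the effects on the study power and to detect differences in the primary outcome", and "Results will be summarized and communicated to the PI, Co-Investigators, DSO, and NIDDK".

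Three other places bear on this:

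- **Blinding.** A.4.2 (Randomization), repeated in A.4.3: "Investigators (except the study statistician) and data collectors will be kept blinded".
- **Alpha.** A.8.3 assigns a type I error of 2.5% to each of the two primary comparisons, "thus keeping overall Type I error rate at 0.05". A.8.1 defines the primary comparison as change at 6 months in non-sedentary minutes and HEI score, between the two arms.
- **Monitoring body.** A.7.5 answers no to a data and safety monitoring board. Oversight rests with the safety officers.

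**The concern.** The sentence gives the evaluation two purposes. One is to see what attrition has done to power, which is legitimate and needs no comparison of arms. The other is to detect differences in the primary outcome, and in this trial the primary outcome is analysed as a between-arm contrast. Nothing in the sentence restricts the evaluation to pooled data, and nothing places it after follow-up ends. Its position among the stopping criteria, and the safety officer among its recipients, point to a time before the end.

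Two things are at stake. The first is blinding. The recipients are the people who run recruitment and follow-up of later cohorts, and no independent board stands between them and the data. Seeing results by arm would be enough to defeat the blind, whether or not anyone acted on them. The second is the error rate. With the full 0.05 committed to the final comparisons, none is left if outcome differences are tested on the way and the trial's course then depends on the result.

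**Working it through.** **1. The plan's own alpha figure.** Two comparisons at 0.025 each (A.8.3): 0.025 + 0.025 = 0.05. The stated overall rate reproduces, and nothing remains for a further test.

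**2. Sidedness of the 0.025.** The protocol does not state it, so I checked it against the stated 88% power for non-sedentary activity. Inputs from A.8.3: 84 centers, 2 classrooms, 4 children per classroom, difference 1 min/h, SD of change 3, ICC 0.10 (center) and 0.07 (provider). Allocation is 1:1.

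- Variance of a center mean, in SD² units: 0.10 + 0.07/2 + (1 − 0.17)/8 = 0.2388
- SE of the difference: √(4 × 0.2388/84) = 0.1066
- Standardised effect over SE: (1/3)/0.1066 = 3.126
- Power, normal approximation, critical value 1.960 (one-sided 0.025): Φ(1.166) = 0.878
- Power, critical value 2.241 (two-sided 0.025): Φ(0.885) = 0.812

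The 88% reproduces only under the one-sided reading, so both readings are carried below.

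**3. What the text fixes about the look.**

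| Feature | Stated in A.7.4? |
|---|---|
| Outcome differences evaluated | Yes |
| Recipients | Yes, including investigators declared blinded |
| Timing or information fraction | No |
| By arm or pooled | No |
| Test, threshold, decision rule | No |

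The information fraction t therefore has to be assumed. I take 0.25 to 0.75.

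**4. Conditional cost of one unadjusted between-arm test.** Under the null hypothesis the interim and final statistics are bivariate normal with correlation √t. With the same critical value c at both, the error per endpoint is 1 − P(|Z₁| < c, |Z₂| < c), with c = 2.241 for two-sided 0.025. The one-sided version uses 1 − P(Z₁ < c, Z₂ < c) with c = 1.960.

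| t | √t | Per endpoint, two-sided 0.025 | Two-endpoint bound (2 ×) | Per endpoint, one-sided 0.025 |
|---|---|---|---|---|
| 0.25 | 0.500 | 0.0465 | 0.093 | 0.0454 |
| 0.50 | 0.707 | 0.0428 | 0.086 | 0.0416 |
| 0.75 | 0.866 | 0.0378 | 0.076 | 0.0367 |

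The last column shows that sidedness barely changes the picture.

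**5. Dependence on endpoint correlation.** The bound in step 4 is a ceiling. At t = 0.50, independent endpoints give 1 − (1 − 0.0428)² = 0.084. If the two endpoints were perfectly correlated, the overall figure would equal the per-endpoint 0.043, which is below 0.05. The protocol gives no correlation, so the overall excess cannot be fixed more closely.

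**6. The pooled case.** Attrition, the pooled SD of change and the pooled ICC carry no arm contrast. Reviewing them spends no alpha and reveals no assignment.

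**The case against.** A reader might infer that the protocol plans a mid-trial efficacy analysis, that it flatly contradicts its blinding statement, and that the overall 0.05 is therefore exceeded. The documents do not support that.

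- No date, test or comparison by arm is stated. Taken literally, pre-post differences are changes from baseline, and A.8.1 names both arms when it means a between-arm test.
- The preceding sentences concern dropout and the attrition allowance, so the author may have meant the power to detect differences after attrition. The participant-compliance part of A.7.1 fits this: retention concerns lead to a discussion of how to preserve power.
- The stopping rules are recruitment and retention only. No efficacy or futility rule appears, although the form's prompt offers efficacy as an example.
- The safety report outline in A.7.1 names no primary-outcome table. Its one unspecified analysis item sits under safety.
- The statistician is exempt from blinding and leads the analysis, so a pooled summary could go to the investigators without harm.
- Boundaries and alpha spending are commonly left to the statistical analysis plan, which is not at hand. Their absence from the protocol is not itself a fault.

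All of this stands, and it makes the error-rate figures conditional. It does not remove the point. If only an attrition check was meant, the clause about detecting outcome differences is unnecessary and authorizes more than intended. No other part of the protocol narrows it. Nor is arm-level information reaching the investigators far-fetched: the same answer has the safety officer, together with the investigators, raise an alert over an excess injury rate in the treatment group.

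**Conclusion.** The point holds as a defect in what the protocol permits, not as proof of a planned interim efficacy test. A.7.4 authorizes an evaluation of primary-outcome differences with no stated timing and no restriction to pooled data, and names recipients who are elsewhere kept blinded. The conflict with blinding becomes real if results are shown by arm. The conflict with the alpha allocation becomes real only if a between-arm test is also made and acted on.

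The sizes in steps 4 and 5 rest on four assumptions: one look, at 25% to 75% of the information, at the same critical value as the final test, with no adjustment. None of these comes from the protocol, so the figures show what the wording leaves open and do not estimate this trial's error rate. The wording should be changed because the change is nearly free and protects both blinding and alpha.

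**What to change.** Replace the two sentences in A.7.4 with text to this effect: *Attrition, the pooled (arm-masked) SD of change and the pooled ICC will be reviewed to re-estimate power. No between-arm comparison of the primary outcomes will be made, or shared with blinded investigators, before the last 6-month visit.*

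If a between-arm look is truly wanted, the protocol should state when it occurs, name an unblinded recipient separate from the investigators, and give a boundary with alpha spending. For illustration, an O'Brien-Fleming boundary with one look at half information tests at about 0.0015 and then 0.0244 (two-sided), which keeps 0.025 per endpoint. A look at 0.001 leaves 0.0246 for the final test.

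The cost is a protocol wording change and the loss of early sight of outcome differences. The modification form reports 43 subjects enrolled, enrollment open and 0 in the interventional part, so as of that submission the change could still be made before 6-month outcomes accrue.
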